## Abstract

**Background:**

Delirium prevalence in the intensive care unit (ICU) is high. Numerous psychotropic agents are used to manage delirium in the ICU with limited data regarding their efficacy or harms.

**Methods/Design:**

This is a randomized controlled trial of 428 patients aged 18 and older suffering from delirium and admitted to the ICU of Wishard Memorial Hospital in Indianapolis. Subjects assigned to the intervention group will receive a multicomponent pharmacological management protocol for delirium (PMD) and those assigned to the control group will receive no change in their usual ICU care. The primary outcomes of the trial are (1) delirium severity as measured by the Delirium Rating Scale revised-98 (DRS-R-98) and (2) delirium duration as determined by the Confusion Assessment Method for the ICU (CAM-ICU). The PMD protocol targets the three neurotransmitter systems thought to be compromised in delirious patients: dopamine, acetylcholine, and gamma-aminobutyric acid. The PMD protocol will target the reduction of anticholinergic medications and benzodiazepines, and introduce a low-dose of haloperidol at 0.5-1 mg for 7 days. The protocol will be delivered by a combination of computer (artificial intelligence) and pharmacist (human intelligence) decision support system to increase adherence to the PMD protocol.

**Discussion:**

The proposed study will evaluate the content and the delivery process of a multicomponent pharmacological management program for delirium in the ICU.

**Trial Registration:**

ClinicalTrials.gov: NCT00842608

## Background

In 2005, approximately 2.7 million Americans aged 65 and older spent at least one day in the intensive care unit (ICU) costing Medicare an estimated $27.5 billion [1-3]. It is estimated that up to 80% of these older ICU patients had delirium during their hospital stay [4]. Older adults with delirium are more prone to falls, injuries, pressure ulcers, restraints, mortality, institutionalization, and dementia [4-8]. Delirium is considered an acute brain failure that is most often unrecognized among older adults in the ICU [9-14]. These patients may receive potentially harmful medications such as anticholinergics and benzodiazepines that are thought to cause or worsen delirium [15-18].

We conducted a systematic evidence review of the existing literature to evaluate the efficacy and safety of various pharmacological interventions [16]. Of the four studies focusing on delirium treatment, only one study suggested a benefit of haloperidol and chlorpromazine in reducing delirium severity, though no differences in delirium incidence, duration, or hospital length of stay were identified [19].

Despite the lack of evidence, clinicians that care for these patients often use typical and atypical antipsychotics, benzodiazepines, and other sedatives to manage the symptoms of delirium [20,21]. This approach conflicts with our current understanding of the neurotransmitter balance in delirium. The available literature suggests a therapeutic role for acetylcholine enhancement, gamma-aminobutyric acid (GABA) reduction, and dopamine reduction [9-12,15,22], which is reflected in available clinical practice guidelines for delirium management [4]. Therefore, this neurotransmitter model supports a combination intervention that includes avoiding or reducing the use of benzodiazepines and anticholinergics, and the use of low dose antipsychotics such as haloperidol [4,23-26]. However, there have been no randomized controlled trials evaluating the efficacy of this approach on reducing delirium severity, duration, or complications [15-18].

Our primary objective is to test the efficacy of a pharmacological intervention in reducing delirium severity and duration among adults cared for in the ICU. Our primary hypothesis is that, in comparison to usual care, intervention patients will have (1) reduced delirium severity at one week following randomization or hospital discharge, and (2) fewer hospital days with delirium or coma. The secondary hypothesis theorizes that the study intervention will result in (1) shorter hospital lengths of stay, (2) lower ICU, hospital, and 30-day mortality, and (3) lower hospital-acquired complications related to delirium.

## Methods/Design

### Ethical Approval

The study has been approved by the Institutional Review Board (IRB) of Indiana University Purdue University Indianapolis. Approval for enrollment in the study requires informed consent provided by the potential participant's legally authorized representative.

### Study Population

Wishard Memorial Hospital (WMH) serves as Indiana's only public acute care hospital for the indigent population with 340 staffed beds, of which 51 are intensive care unit beds. The ICU at WMH includes a medical ICU (MICU), surgical ICU (SICU), coronary ICU (CCU), and progressive ICU (PICU). In 2008, WMH provided 88,502 patient days of care throughout all hospital beds. The general population demographics of patients admitted to WMH include 59% African-Americans and 68% females [27]. Demographics of patients admitted to critical care units at WMH are included in Table 1.

**Table 1 T1:** Demographic summary of WMH ICU population

Variable	SICU	MICU + CCU	PICU
**Number of beds**	8	14	29

**Average monthly admission**	40	67	228

**Female**	35%	38%	42%

**Age**			
- **< 60**	72%	71%	70%
- **61-80**	27%	25%	26%
- **> 80**	1%	4%	4%

**Admitted from**			
- **ER**	55%	61%	52%
- **Non-ICU wards**	20%	19%	12%
- **Other**	1%	20%	36%

**Mean length of ICU stay, days**	5.96	6.10	3.72

**Discharge location**			
- **Home or other facility**	12%	14%	38%
- **Regular hospital wards**	29%	22%	51%
- **PICU**	47%	50%	--
- **Other**	12%	12%	11%

**ICU mortality rate**	11%	12%	1.3%

*SICU = Surgical intensive care unit; MICU = Medical intensive care unit; CCU = Coronary care unit; PICU = Progressive intensive care unit; ER = Emergency room

### Enrollment and Eligibility

Patients admitted to the ICU for at least 24 hours will be eligible for screening for the study. Screening measures, further described below, will include a measure of the level of sedation using the Richmond Agitation-Sedation Scale (RASS) [28] and the Confusion Assessment Method for the ICU (CAM-ICU) to evaluate for delirium [29]. Criteria for inclusion in the study consist of: (1) patients admitted to any WMH ICU ward (SICU, PICU, MICU, CCU) for ≥ 24 hours, (2) aged ≥ 18 years, (3) score positive for delirium based on the RASS and CAM-ICU on any day during the ICU stay, and (4) are English-speaking. Patients are excluded for a history of severe mental illness, admission with an alcohol-related delirium, admission for an aphasic stroke, have a history of allergic reaction or contraindication to haloperidol, are pregnant or nursing, or have previously been enrolled in the study.

Patients meeting inclusion criteria will be pursued for informed consent by contacting a legally authorized representative. Figure 1 describes the flow of patients through the screening and enrollment plans of the study. As seen in Figure 1, we anticipate approaching approximately 4700 patients for screening in order to enroll 428 in the randomized controlled trial.

**Figure 1 F1:**
[figure not shown]
**Expected PMD recruitment flow chart**. ICU: Intensive Care Unit; WMH: Wishard Memorial Hospital; RASS: Riker Agitation Sedation Scale; CAM-ICU: Confusion Assessment Method for the Intensive Care Unit

### Design and Delivery of the Intervention

In 2005, we utilized the information technology infrastructure at WMH to develop a patient-specific computerized decision support system (CDSS). This system targeted hospitalized older adults with cognitive impairment (CI), including those with delirium. This study was called enhancing care for hospitalized older adults with memory problems (e-CHAMP). The intervention was designed to: (1) alert the clinician of the presence of CI in his/her patient at the time of ordering a diagnostic or therapeutic order; (2) identify a medication order with a moderate to severe central anticholinergic activity and suggest an alternative medication; (3) identify the presence of bladder catheterization and suggest an early discontinuation; and (4) identify a physical restraint order and suggest pharmacological alternatives using a low dose of haloperidol [30].

This prior clinical trial experience revealed valuable lessons that translated to the design of the current CDSS in the intensive care setting. First, many alerts were not routinely updated, and often presented conflicting or confusing recommendations that were outdated. Second, the end-users were bombarded with numerous computer-generated alerts and reminders during their routine care of hospitalized older adults [31,32]. The reputation for the clinical relevance of these computer-based alerts, warnings, and reminders was poor amongst clinicians. Furthermore, the end-users developed what was referred to as the "F8" or "escape" button reaction, where the end-user automatically ignored the alerts. Thus, we know that computer-based decision support may be a useful resource, but by itself cannot change provider behavior in our institution.

In response to the e-CHAMP experience, we elected to support the computerized delivery of the study intervention with human intelligence in designing the current trial, the Pharmacologic Management of Delirium (PMD). Realizing the pace of care in the ICU environment is rapid and changes quickly, the constantly present computerized component described below will be activated for each study patient enrolled in the intervention arm. In addition, a clinical pharmacist with training in cognitive impairment and delirium ([name]) will review medication orders twice daily to carry out the study intervention. The inclusion of a clinical pharmacy specialist will allow for review of medications that may be ordered prior to enrollment in the study as well as identifying medications that may be ordered outside of the capabilities of the CDSS, such as non-formulary drugs. Additionally, the inclusion of a human interaction will improve adherence to study interventions as well as document reasons for protocol deviations.

#### Infrastructure of the Computerized Intervention: The Medical GOPHER Physician Order-Entry System

Since 1984, the Medical GOPHER system, a network of computer workstations, has allowed physician order entry and other direct interactions between computer and physician [33]. The Medical GOPHER system is used by physicians to write all orders at WMH and is linked to the Regenstrief Medical Record System (RMRS). It allows the computer to push information to providers as a CDSS. Furthermore, it can do this at the critical time of clinical decision making, while the physician is initiating an order or recording a diagnosis. The study intervention will utilize the GOPHER system to alert any practitioner entering an order (either original or verbal) for any of twenty medications with definite or strong anticholinergic properties that the patient is enrolled in the study and the medication is not recommended. Additionally, the intervention will provide a list of alternatives to consider depending on the intended use of each particular medication.

#### Regenstrief Medical Record System at WMH

The computerized Regenstrief Medical Record System (RMRS) is the primary instrument for processing data and monitoring patient and physician activity at WMH. RMRS is a modular system, capable of recording appointments, laboratory, pharmacy, and physician ordering activity. This comprehensive database captures all inpatient and outpatient data by date in a fully coded form, making patient care data readily retrievable. Additionally, RMRS contains death certificate information for registered patients who die in, or outside of, Indiana. The RMRS will be used to evaluate secondary study outcomes such as length of stay and mortality.

### Description of the Pharmacologic Intervention

The study intervention targets the imbalance of three neurotransmitters believed to play a role in delirium. Our intervention will focus on the pharmacologic contribution of those neurotransmitter systems through a combination of human and electronic activity. The CDSS will be employed in reducing the role of anticholinergic medications in delirium, whereas the human interaction by the study pharmacist will execute benzodiazepine monitoring, initiate haloperidol as described below, and ensure adherence to anticholinergic reduction recommendations provided by the CDSS.

#### Reduction of anticholinergic medications

Using lists of medications with central anticholinergic activities identified from the medical literature well as values of serum anticholinergic activity (SAA) measurement, our interdisciplinary aging brain team developed the Anticholinergic Cognitive Burden (ACB) scale. The scale is intended to be a practical tool to identify the severity of negative anticholinergic effects on cognition of prescribed and over-the-counter medications. The team established the following scoring system: drugs with possible anticholinergic effects (as demonstrated by the SAA or the in-vitro affinity to muscarinic receptors but with no clinically relevant negative cognitive effects) were given a score of 1. Drugs with established and clinically relevant cognitive anticholinergic effects were given the score of either 2 or 3, based on each drug's blood-brain permeability and its association with the development of delirium identified in available literature [12].

Medications included in the ACB having a score of 2 or 3 will be the targeted medications for anticholinergic burden reduction. Each order for a definite anticholinergic will trigger a warning message to avoid its use in patients with delirium, along with alternative recommendations and prompts to discontinue the offending agent. The definite anticholinergics targeted in our study as well as suggested alternatives are available in Appendix 1.

#### Benzodiazepine reduction

Withdrawal of benzodiazepines in intervention patients will follow recommendations from the Society of Critical Care Medicine (SCCM) guidelines regarding the use of sedative and analgesic medications in critically ill patients [4]. Benzodiazepine reduction will occur cautiously but deliberately, with constant communication with the primary medical or surgical team and with close monitoring for intolerable withdrawal reactions. Benzodiazepine dose reductions will be initiated with 20-40% dose reduction on day one, with subsequent reductions of 10-25% every 24 hours as tolerated. Safety and tolerability of the weaning schedule will be evaluated through routine nursing assessments of vital signs and behavior documented every four hours.

#### Low-Dose Haloperidol course

During the ICU stay, every patient who consents to the study, randomized into the intervention group, and is not under mechanical ventilation will received an order of 0.5 to 1 mg haloperidol every 8 hours via oral or parental route for a total of seven days or until discharge from the hospital. Because of age-related pharmacokinetic differences in metabolism and pharmacodynamic sensitivity, patients under the age of 60 years will be given 1 mg/dose, and those aged 60 years or older will be given 0.5 mg/dose. This low dose of haloperidol is based on the critical analysis of the data from the clinical trials that tested the use of antipsychotics in delirium and the drug metabolism of psychotropics in older adults. This low dose is not intended to replace the sedative regimen used in patients receiving mechanical ventilator.

Intravenous haloperidol use has been associated with a higher risk of cardiovascular adverse outcomes, specifically QT prolongation and Torsades de Pointe. However, in a recent systematic review of case reports of haloperidol-associated arrhythmias, a wide range of haloperidol doses were used prior to the inciting events (2-1540 mg). The onset of most events was typically within minutes to hours following the cumulative doses of haloperidol (range 15 minutes to 5 days). The authors concluded that haloperidol given intravenously appears safe when given in doses less than 2 mg. Patients enrolled in our study will not be given haloperidol if they have: (1) a QT prolongation of 500 milliseconds or above, (2) a history of seizure disorders, or (3) an indication for seizure prophylaxis (i.e., severe stroke or traumatic brain injury) as haloperidol may decrease the seizure threshold [34].

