### Randomization

Following the eligibility and screening assessments, informed consent will be obtained from the participant's legally authorized representative. Randomization of eligible patients providing consent will occur in a 1:1 ratio between intervention and usual care groups. The computerized order entry system (GOPHER) is capable of performing this process and will conduct randomization in random blocks of four to encourage even distribution of patients between the intervention and usual care groups.

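### Haloperidol depends on ventilation status, so the pooled estimate averages a three-part and a two-part package, and neither named primary analysis takes ventilation into account

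*Protocol article*

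**What the plan says.** All references are to the protocol article.

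- **Abstract, Methods/Design.** The intervention is presented as one three-part protocol that will "introduce a low-dose of haloperidol at 0.5-1 mg for 7 days". No ventilation condition is mentioned.
- **Low-Dose Haloperidol course.** The order is conditional: it goes to a patient who is "randomized into the intervention group, and is not under mechanical ventilation". The section adds "This low dose is not intended to replace the sedative regimen used in patients receiving mechanical ventilator". Haloperidol is also withheld on other grounds: "Patients enrolled in our study will not be given haloperidol if they have: (1) a QT prolongation of 500 milliseconds or above", a seizure history, or an indication for seizure prophylaxis.
- **Benzodiazepine reduction.** "Withdrawal of benzodiazepines in intervention patients will follow recommendations from the Society of Critical Care Medicine (SCCM) guidelines". Neither this component nor the anticholinergic one is tied to ventilation.
- **Enrollment and Eligibility.** The trial takes "patients admitted to any WMH ICU ward (SICU, PICU, MICU, CCU) for ≥ 24 hours". Ventilation is not an exclusion.
- **Randomization.** Allocation is 1:1 in "random blocks of four to encourage even distribution of patients between the intervention and usual care groups". No stratum is named.
- **Data Analysis.** The analyses are by intention to treat. The day-8 severity ANCOVA has the baseline score as its only covariate, and treatment by baseline score is the only interaction considered. Coma-free and delirium-free days are compared by an unadjusted t-test with a Wilcoxon check, followed by a regression on patient characteristics that are not named.
- **Discussion.** The target is the combined intervention, with no attempt to separate components. The low haloperidol dose and the lack of an absolute ban on the other drugs are listed as limits on the effect. The ventilation condition is not.

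**The concern.** One of the three components is switched by a patient characteristic that can be observed in both arms before randomization. While ventilated, an intervention patient is assigned two components; a patient who is not ventilated, and has no other bar to haloperidol, is assigned three. The share of each is not given, so a reader of the final result would not know how far the pooled estimate speaks for the package that the abstract describes.

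The usual-care arm may receive haloperidol without restriction, so in ventilated patients the protocol itself adds no haloperidol contrast.

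Ventilation is also a plausible predictor of coma-free and delirium-free days. It goes with sedation, as the haloperidol section itself notes, and the duration outcome counts coma days and days after death as failures. The article gives no figure for this association, so its strength is an assumption. If it exists, the named primary analyses give up some precision and leave a chance imbalance uncorrected.

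**Working it through.** **Inputs.** From the article: 428 patients, 1:1, so 214 per arm; overall significance level 0.05. Assumed: two-sided testing; ventilated share v from 10% to 70% (not given); a shift b = 0.5 SD in the outcome between ventilated and non-ventilated patients (not given).

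**1. The plan's own figure.** The article gives no effect size, SD or power with 428, so it cannot be reproduced. Solving backwards, the detectable standardized difference is (1.960 + z_power) × √(2/214), where √(2/214) = 0.0967. This gives 2.802 × 0.0967 = 0.271 at 80% power and 3.242 × 0.0967 = 0.313 at 90%. These serve only as a scale for step 5.

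**2. What the pooled contrast estimates.** Pooled effect = (1 − v) × E3 + v × E2, where E3 is the effect under three components and E2 the effect under two. This treats status as fixed and ignores the QT and seizure criteria. The article states neither v nor how far E2 falls below E3, so a pooled result cannot be translated into E3.

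**3. Validity of the pooled test.** Blocks of four without strata were simulated 20,000 times with no treatment effect and b = 0.5:

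| v | bias (SD) | type I error |
|---|---|---|
| 30% | −0.0009 | 0.0485 |
| 50% | −0.0003 | 0.0499 |

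Leaving ventilation out does not bias the pooled comparison or inflate its error rate.

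**4. What adjustment would gain.** Variance inflation from omitting ventilation is b²v(1 − v) relative to the within-group variance. The SD of the between-arm difference in ventilated share is √(v(1 − v) × 2/214), and 1.96 times this gives the 95% range.

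| v | b²v(1 − v), b = 0.5 | 95% chance imbalance |
|---|---|---|
| 10% | 0.25 × 0.09 = 2.3% | ±5.7 points |
| 30% | 0.25 × 0.21 = 5.3% | ±8.7 points |
| 50% | 0.25 × 0.25 = 6.3% | ±9.5 points |
| 70% | 0.25 × 0.21 = 5.3% | ±8.7 points |

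An imbalance of 9.5 points with b = 0.5 moves the unadjusted difference by 0.5 × 0.095 = 0.047 SD, about half of the standard error of 0.0967. In the ANCOVA the gain would be smaller to the extent that the baseline score already carries the same information.

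**5. What a subgroup analysis could show.** The standard error of the difference between stratum effects is √(2/(214(1 − v)) + 2/(214v)). Take E3 = 0.271 SD. At v = 50% the standard error is √(2/107 + 2/107) = 0.193.

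- Ventilated effect zero: Φ(0.271/0.193 − 1.96) = 29%. At v = 30% this is 25%, and at v = 10% it is 13%.
- Ventilated effect half of E3: 10% at v = 50%.
- With E3 = 0.313 SD, the ceiling at v = 50% is Φ(0.313/0.193 − 1.96) = 37%.

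The subgroup estimates would be descriptive.

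**The case against.** **A null result would be uninterpretable.** A reader might infer this from a pooled estimate over two packages. The documents do not support it. The analyses are by intention to treat, the Discussion declares the combined intervention as the target, and step 3 shows an unbiased pooled contrast with the right error rate. A null result is interpretable for the strategy as delivered; what it does not readily support is a statement about the full three-part protocol.

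**The trial tests two different interventions, with ventilation deciding haloperidol altogether.** This is also too strong. Two of the three components are common to all intervention patients. QT prolongation and the seizure criteria withhold haloperidol too. The text ties the order to not being ventilated during the ICU stay and leaves open whether it follows extubation.

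**The trial is underpowered because of dilution.** The ventilated share, haloperidol's share of the effect and the starting power are all absent from the article, and nothing says that 428 was sized for an undiluted effect. Any such loss would come from the treatment rule, and neither stratifying nor adjusting would recover it. No power loss is claimed here.

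**The article is condensed, and an analysis plan could name ventilation.** This stands in part. The unnamed patient characteristics in the later regression could include it, and a stratum could be described elsewhere. But the primary methods are stated: the baseline score is the only ANCOVA covariate, and the leading duration test is unadjusted. The point is an improvement on those stated methods.

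**Stratification is not needed.** This stands. Ventilation status at randomization is a baseline variable, so comparisons within its levels remain randomized once it is recorded. Chance imbalance of this size is ordinary and already reflected in the standard error.

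**Conclusion.** The point holds as a minor but concrete improvement. The haloperidol order depends on ventilation, ventilated patients are eligible, and neither named primary analysis takes this into account, so the pooled estimate averages a three-part and a two-part package in unstated proportions. The primary inference on the delivered strategy is sound.

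What is lost is limited to three things: some precision (2-6% of variance if b = 0.5 SD and v is 10-70%, both assumed), protection against chance imbalance (95% range about 6 to 9.5 points), and a planned estimate in patients not ventilated at randomization. The Discussion also omits the ventilation condition from its limits on the effect, and the article does not say whether the order applies after extubation.

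**What to change.** - Record mechanical ventilation status at randomization in both arms.
- Add it as a covariate to the day-8 ANCOVA, and replace the unadjusted t-test as the leading duration analysis with a regression containing treatment and ventilation status. The Wilcoxon check can stay. Stratifying the GOPHER blocks by ventilation is optional.
- Keep the pooled intention-to-treat comparison primary. Pre-specify the treatment effect by baseline ventilation status as a descriptive subgroup, with an interaction test.
- Report the share of intervention patients who received haloperidol, overall and by baseline ventilation status.
- Add the dilution to the limitations, and align the abstract with the conditional order.
- State whether the haloperidol order applies after extubation. Which rule applies is for the investigators to settle.

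The cost is one recorded binary variable, one model term and a few lines of text. Two downsides remain: the interaction test has low power (step 5), and baseline status will not cleanly separate haloperidol recipients from non-recipients, because ventilation can change after randomization and other criteria also withhold the drug.
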